### Handling of Missing Data

Patients who fail to appear for the MRI, EOS, or AE test with the Inmodi knee brace will be invited again. After the second miss, they will be excluded (and replaced if the recruitment phase is still ongoing). Missing source data from MRI or EOS are not expected. In the case of missing readouts in the electronic case report form, the radiologist is asked to do the missing readout or to give reasons for the missing.

In case of unexpected data loss or data damage with the Inmodi brace data collection, the participant will be reinvited.

Concerning PROMs, a maximum of 2 missing items is allowed in OKS. They will be imputed with the mean of all other responses. In case of additional missing items, the patient will be contacted to clarify. For COMI and UCLA, missing data will not be imputed. The patient will be contacted for clarification. For KOOS: If more than 50% of subscale items are missing, the subscale score cannot be calculated. Otherwise, the sum of the items answered is normalized to 0‐100. For FJS-12, if more than 4 of the answers are missing, the total score cannot be calculated. With fewer items missing, these can be replaced by the mean of the items answered. Generally, if a patient makes more than one entry for a question, the worst applies.

### Ethical Considerations

An ethical permit was granted for this study by the Business Administration System for Ethical Committees (BASEC No.: 2022‐01699) from the ethics committee of Canton Zurich, and written informed consent was obtained from all subjects after the nature and possible consequences of the studies were explained. The participants did not receive any compensation. All study data were stored in a password-protected REDCap database where participants are only identified by a unique identifier. A key list is kept secure by the project leader. An integrated audit trail system maintains a record of initial entries and changes (reason for change, date and time of change, and user identification). All procedures performed in this study were developed internally to suit our specific clinical context and have been validated through prior successful implementation [41] and are in line with the 1964 Helsinki Declaration and its amendments. This study was registered at Clinicaltrials.gov with study identifier NCT06351059.

## Results

Recruitment and data collection started in December 2022. In November 2023, data collection has been completed for the first visit. The data collection for the second visit will end in 2024. Data processing and analysis are ongoing at the time of this writing.

Baseline data of study participants are shown in Table 3. The median age for the healthy controls (A) is slightly lower, and for the TKA group (D) slightly higher compared to the 2- and 5-year postoperative patients (B and C). Older patients in the TKA group (D) are reasonable, as TKA surgery is often the last option left for treatment. We do observe higher values for BMI in the poor postoperative outcome groups (B2 and C2) and the TKA group (D). Balanced sex distribution was not achieved in 2- and 5-year postoperative groups due to the low willingness to participate as well as the low numbers of female patients within our registry meeting all the inclusion criteria.

**Table 3. T3:** Baseline data of study participants.

Characteristic	A (n=20)	B1 (n=20)	B2 (n=20)	C1 (n=20)	C2 (n=20)	D (n=20)
Age, mean (SD)	46 (7)	50 (8)	54 (8)	52 (7)	52 (7)	67 (7)
BMI, mean (SD)	24.25 (2.82)	24.75 (2.75)	26.05 (2.44)	24.65 (2.31)	26.00 (3.71)	26.35 (3.99)
Sex, n (%)						
Female	10 (50)	9 (45)	8 (40)	6 (30)	6 (30)	10 (50)
Male	10 (50)	11 (55)	12 (60)	14 (70)	14 (70)	10 (50)

## Discussion

### Principal Findings

This exploratory study aims to identify biomarkers with a prognostic value in the prediction of osteoarthritis. Acoustic, kinematic, and thermal features will be extracted and combined with an artificial intelligence algorithm, and evaluated against gold-standard osteoarthritis diagnosis, such as radiographs and MRI. Some candidate acoustic biomarkers have been identified in a preliminary study [9], using a multifractal analysis method. However, multiple other candidates will be evaluated individually or in combination in our study. Therefore, the primary endpoint can be defined as the area under the curve of the receiver operating characteristic analysis of each biomarker or combination of biomarkers in the regression analysis, finally identifying the parameters with the highest sensitivity and specificity to predict early-stage osteoarthritis in clinical use. AE is patient-dependent, and as such, demographic and baseline health data will be captured and entered as covariates in the regression models. The secondary objective is to evaluate the value of these biomarkers in predicting osteoarthritis evolution. For this objective, the patients will be examined a second time at 9-month intervals, and the new biomarkers will be introduced in regression models to evaluate the predicted performance for osteoarthritis evolution.

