**Objective:**

This study aims to identify acoustic biomarkers with prognostic value for the early detection of osteoarthritis. To achieve this, a preliminary reference database will be developed using a subpopulation at risk of developing osteoarthritis, incorporating acoustic signals and gold-standard clinical measures for validation.

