**Methods:**

A total of 100 patients with previous reconstructive knee surgery and 20 healthy controls will be examined twice at a 9-month interval for both knees. Acoustic emissions (AE) will be recorded with the Inmodi knee brace (École Polytechnique Fédérale de Lausanne; EPFL) during 4 functional tests (unloaded flexion-extension, sit-to-stand test, one-step test, and walk test). Gold-standard osteoarthritis diagnostics will be assessed and evaluated by an experienced radiologist for (1) the magnetic resonance imaging (MRI) Osteoarthritis Knee Score (MOAKS) and (2) the Kellgren-Lawrence (KL) grading scores. Feature analysis and multivariate modeling will be used to study the association between the extracted sound parameters and osteoarthritis (MOAKS and KL). In addition, thermal images will be taken to investigate the state of inflammation. Participants will fill out 5 health-related questionnaires (Oxford Knee Score [OKS], Core Outcome Measures Index [COMI], University of California at Los Angeles [UCLA ]activity scale, Knee Injury and Osteoarthritis Outcome Score [KOOS], and Forgotten Joint Knee Score-12 [FJS-12]) at both time points.

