## Methods

### Project Design

This is a prospective, single-center, exploratory study. A cross-sectional and a longitudinal dataset will be collected. A total of 120 participants will be recruited and examined twice at a 9-month interval at the Schulthess Klinik in Zurich (see Table 1 for the measurement procedure). The cross-sectional dataset stems from the first visit of the participants and serves for the identification of AE biomarkers for osteoarthritis. The longitudinal dataset combines the data from the first and second visits and tests whether the osteoarthritis changes can be assessed from the biomarkers. A secondary aim is to evaluate the ability of the AE biomarkers from the first visit to predict the condition’s progression as observed during the second visit.

**Table 1. T1:** Summary table with all project visits, including relevant procedures and timelines.

Study period	Information	Screening	1st visit	2nd visit
Time point	Precall (maximum 2 months)	0	0-2 months	9 months (±2 months)
Oral and written information	✓			
Written consent		✓		
Check inclusion/ exclusion criteria		✓		
Anthropometric and patient data			✓	✓
EOS radiography			✓	✓
MRI^a^			✓	✓
Acoustic emission test with Inmodi knee brace			✓	✓
PROMs^b^ (at home)			✓	✓

a MRI: magnetic resonance imaging.

b PROM: patient reported-outcome measurement.

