### Feature Extraction

This stage involves the calculation of the outcome parameters that will allow the distinction of different osteoarthritis grades. We will initially rely on state-of-the-art parameters in audio classification, such as spectral analysis (mel-frequency cepstrum coefficients [MFCC]) [36,37] and fractality (the First log-cumulant of the scaling exponent, Global Holder Exponent; paper submitted), average level, peak magnitude (peak amplitude) [38] and click patterns (number of clicks/hits), and number of clicks passing threshold [39].

We will also explore the development of novel features specifically oriented to osteoarthritis classification, such as matched filters of prototype sounds [40].

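### The primary AUC may range over combinations of acoustic, kinematic and thermal features, while the objective and conclusions concern acoustic biomarkers; nothing stated isolates what sound contributes

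*Protocol article*

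**What the plan says.** All references are to the protocol article.

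**Acoustic only.** The abstract's objective reads "This study aims to identify acoustic biomarkers with prognostic value for the early detection of osteoarthritis". Under Project Design, the first-visit dataset "serves for the identification of AE biomarkers for osteoarthritis", and the secondary aim is to "evaluate the ability of the AE biomarkers from the first visit to predict" progression. The abstract's Methods models sound parameters against MOAKS and KL and mentions temperature separately: "thermal images will be taken to investigate the state of inflammation". Feature Extraction opens with "We will initially rely on state-of-the-art parameters in audio classification" and lists only audio features. Feature Analysis and Multivariate Modeling correlates AE parameters with the gradings. Under Signal Segmentation and Denoising, kinematic data serve to cut the audio into movement phases. The abstract's conclusions and the closing Conclusion are about acoustic biomarkers and a knee-sound tool.

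**Three modalities.** Principal Findings says "Acoustic, kinematic, and thermal features will be extracted and combined with an artificial intelligence algorithm, and evaluated against gold-standard osteoarthritis diagnosis". Three sentences later, "the primary endpoint can be defined as the area under the curve of the receiver operating characteristic analysis of each biomarker or combination of biomarkers". Relevance of the Project likewise describes a platform that combines biomarkers from each modality.

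**The concern.** The section that defines the primary endpoint allows a wider index test than the sections that describe the analysis. As worded, the combination with the highest sensitivity and specificity may contain acoustic, kinematic and thermal features in any proportion. If that combination is the main result, its AUC measures how well the whole sensor set classifies knees. Whether knee sound carries information about osteoarthritis is a different question, and it is the one that the objective asks and the conclusions intend to answer. At stake is the attribution of the result: a good combined AUC could be reported under an acoustic-biomarker heading without anyone having shown that the microphones added to it.

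**Working it through.** **1. The only power figure in the article.** Project Population gives 0.25 as the smallest detectable correlation with n = 120, 80% power and a significance level of .05 (two-sided assumed here).

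- Formula: r = tanh((z₀.₉₇₅ + z₀.₈₀)/√(n − 3)).
- Numbers: (1.960 + 0.842)/√117 = 2.802/10.817 = 0.259; tanh(0.259) = 0.253.

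The stated 0.25 reproduces. It is framed as estimating KL grade from the AEs, so it too assumes an acoustic-only predictor and says nothing about a three-modality algorithm.

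**2. The sections side by side.**

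| Section | Predictors named |
|---|---|
| Abstract, Objective | acoustic |
| Abstract, Methods | sound parameters; thermal images for inflammation |
| Project Design | AE, for both the cross-sectional and the secondary aim |
| Feature Extraction | audio features only |
| Feature Analysis and Multivariate Modeling | AE parameters |
| Abstract, Conclusions; Conclusion | acoustic |
| Relevance of the Project | biomarkers from each modality, combined |
| Principal Findings (primary AUC) | acoustic, kinematic and thermal, combined; then each biomarker or combination |

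**3. What the stated analyses would show about sound.**

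- Single-feature AUCs: the value of one acoustic feature at a time, not of a multivariate acoustic model.
- Feature importance from tree ensembles: the use that one fitted model makes of each feature, not the AUC gained by adding sound.
- Limitations: the relation of acoustic biomarkers to movement, and possible adjustment for load imbalance. No counterpart for temperature is described.

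**4. How little a combined AUC can reveal.** No modality-specific AUC is given in the article, so every input here is assumed. Take equal-variance binormal scores that are independent between modalities, and let z = Φ⁻¹(AUC). The best linear combination of an acoustic score (a) and a kinematic-plus-thermal score (k) has

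AUC_comb = Φ(√(z_a² + z_k²)).

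With k = 0.80, z_k = 0.842 and z_k² = 0.708:

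| Acoustic AUC | z_a² | √(z_a² + z_k²) | Combined AUC |
|---|---|---|---|
| 0.50 | 0 | 0.842 | 0.800 |
| 0.55 | 0.016 | 0.851 | 0.803 |
| 0.60 | 0.064 | 0.879 | 0.810 |
| 0.65 | 0.148 | 0.926 | 0.823 |

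With the acoustic AUC held at 0.60 and k varied: k = 0.70 gives 0.720, k = 0.75 gives 0.764 and k = 0.85 gives 0.857. The gain from sound is 0.020, 0.014 and 0.007.

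Entering kinematic and thermal scores separately at 0.70 each, the combined AUC is 0.771 when the acoustic AUC is 0.50, 0.783 when it is 0.60 and 0.818 when it is 0.70.

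**The case against.** The case on the other side has several good parts.

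- The endpoint covers each biomarker as well as combinations, and the modelling section also analyses features individually. Acoustic AUCs will therefore exist. This stands, but they are single-feature AUCs, and the text does not say which AUC supports the conclusion.
- The rest of the Principal Findings paragraph speaks of acoustic candidates and justifies covariates by the patient dependence of AE, so an acoustic reading is possible. It is possible but not secured, because the preceding sentence names three modalities.
- The multimodal scope is declared in Relevance of the Project, where the aim is to explore the Inmodi system. This stands: a combined model answers that aim and should be kept.
- Feature-importance analysis, the examination of movement patterns, and the promise of open feature sets and code make silent misattribution less likely. This also stands. None of them yields an acoustic-only multivariate AUC or an increment, and none addresses temperature.
- The study is exploratory and the article is condensed. Details of model comparison can be left to a fuller document, but the difference between the stated endpoint and the stated objective is in the article itself.

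A reader might infer that temperature and kinematics separate diseased from healthy knees on their own, or that the primary result cannot answer the study's question. The article supports neither. It gives no discrimination figures for those sensors, and the endpoint as worded includes acoustic AUCs along with combined ones.

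**Conclusion.** The inconsistency is real, and its consequence is limited but worth correcting. The primary AUC is defined over features that may come from three modalities, while the objective, the described analysis and the conclusions concern sound. A combined AUC alone would not answer the acoustic question, and nothing stated isolates the multivariate acoustic contribution. Misattribution is a risk, not a certainty.

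The size is illustrative only. Under independent binormal scores and an assumed kinematic-plus-thermal AUC of 0.80, a combined AUC of 0.80 to 0.82 is compatible with an acoustic AUC anywhere from 0.50 to 0.65. Independence is a convenience: the Limitations section itself raises the possibility that sound reflects movement, and correlated scores would change these values. The point about definition does not depend on them.

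**What to change.** Reconcile Principal Findings with the Objective, Project Design, Feature Extraction, and Feature Analysis and Multivariate Modeling:

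1. State that the AUC supporting the acoustic-biomarker conclusion is the cross-validated AUC of models built from acoustic features only.
2. Report the kinematic-plus-thermal model and the three-modality model alongside it, in the same leave-one-subject-out folds.
3. Give the AUC difference, all three modalities minus kinematic plus thermal, with an interval obtained at participant level (for example by bootstrapping participants), since both knees of each participant are measured.
4. Keep the combined model as the answer to the Inmodi-platform aim in Relevance of the Project.

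Adding kinematic and thermal features to the Methods would also make the text consistent, but would leave the acoustic conclusion without a result of its own.

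The cost is a rewording and a few extra model fits on measurements that the study already makes. The downside is that the headline AUC may be lower than that of the combined model.

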### Relevance of the Project

A wearable device was developed at the École Polytechnique Fédérale de Lausanne (EPFL) for collecting and processing acoustic and kinematic signals. This device—called the Inmodi knee brace—collects airborne acoustic data from the medial and lateral subpatellar areas and kinematic information from the thigh and the calf, both modalities synchronously [17,18]. The platform is then complemented by thermal information of the knee as a measure of inflammation and uses artificial intelligence–based data analysis to extract and combine relevant biomarkers of joint function from each modality. Preliminary data suggests that this combined approach may enable a noninvasive early diagnosis of osteoarthritis. A preliminary *in vitro* animal study with horses’ legs showed a strong association between the joint condition and the power of acoustic emission (AE) signals analyzed [19]. Recently, we tested a prototype of the Inmodi knee brace in 17 patients from our clinic shortly before total knee arthroplasty (TKA). These patients endured severe osteoarthritis on the leg undergoing surgery and mild to moderate on the contralateral one. A machine learning (ML) algorithm was able to discriminate the leg states with a specificity of 0.96 (perfect=1; data not yet published).

The aim of this pilot project is to further explore the potential of the Inmodi system to diagnose osteoarthritis at earlier stages. Therefore, we will develop a preliminary reference database in a subpopulation at risk of developing osteoarthritis, while following recent recommendations [20]. The identification and validation of novel biomarkers with a ML algorithm require a training dataset and a test dataset, both with potential biomarkers and gold-standard clinical outcomes for validation. This database will require a sample size large enough to be statistically sound to prevent statistical overfitting. Unfortunately, power analysis is not possible for most ML methods, due to the impossibility of guaranteeing statistical assumptions on the distributions of the features and their linear and nonlinear dependencies. That is why we rely on leave-one-subject out nested cross-validation for assessing the statistical relevance of the resulting models. This is the most conservative and robust cross-validation strategy for overfitting. The specific sample size of 120 was considered as feasible within the time constraints of the project.

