### Feature Analysis and Multivariate Modeling

In this stage we will study the association between the extracted parameters and osteoarthritis (using the KL or MOAKS grading as the dependent variable), both individually for each feature and also by creating linear and nonlinear multivariate models. For this, we will follow a strategy guided by the principles of (1) increasing complexity and (2) clinical explainability. Thus, the initial models we consider are linear discriminant analysis and logistic regression, which would be ideal options in case we have a reduced number of highly informative and discriminative features. In this ideal scenario, the models would be highly interpretable and easily translatable to a clinical description. In case more sophisticated models are required, we prioritize ensembles of decision trees, such as random forest and gradient boosting, due to the possibility of performing advanced feature importance analysis and derivation of statistical decision rules.

All features will be tested for normality by Shapiro-Wilk tests and presented as mean (SD; normally distributed data) or median and range and, if needed, in histograms, box plots, or violin plots (nonnormal data).

Associations between AE parameters and osteoarthritis (KL or MOAKS grading) will be evaluated using Pearson (normally distributed data) or Spearman (nonnormal data) repeated measures correlation coefficients, as well as with logistic regression models. Mixed ANOVA will be used to compare differences in the AE, osteoarthritis grading parameters between groups. Also, we will specifically assess the relevance of potential confounding variables such as BMI, age, activity level, and gender. The significance level will be set to *P*=.05, and due to the potentially large number of tests, we will apply the Holm post-hoc correction to all *P* values. For multivariate models, the statistical association will be characterized using leave-one-subject-out nested cross-validation, with a subsequent estimation of a confidence interval for prediction accuracy. This is the most conservative and robust cross-validation strategy for overfitting , and with our sample size (n=120), we will have a good estimation of the model variance. Statistical analyses will be done with R (version 4; R Foundation), Matlab (version 2021b or higher; MathWorks, Inc), and Python (version 3.6 or higher; Python Software Foundation).

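### The primary endpoint is the AUC, but parameters are finally chosen on sensitivity and specificity at an unspecified cut-off, and the stated cross-validation does not clearly cover single biomarkers

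*Protocol article*

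**What the plan says.** Three places in the protocol article bear on this.

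- **Endpoint** (Discussion, Principal Findings): "the primary endpoint can be defined as the area under the curve of the receiver operating characteristic analysis of each biomarker or combination of biomarkers". Candidates are not limited to multi-feature models: "multiple other candidates will be evaluated individually or in combination in our study".
- **Final choice** (same sentence as the endpoint): "finally identifying the parameters with the highest sensitivity and specificity to predict early-stage osteoarthritis in clinical use". No cut-off, and no rule for finding one, is given.
- **Validation** (Methods, Feature Analysis and Multivariate Modeling): associations are studied "both individually for each feature and also by creating linear and nonlinear multivariate models". The held-out procedure follows: "For multivariate models, the statistical association will be characterized using leave-one-subject-out nested cross-validation, with a subsequent estimation of a confidence interval for prediction accuracy". For features taken one at a time, that section names correlations, logistic regression and Holm-corrected P values, but no cross-validation. The Introduction (Relevance of the Project) speaks more generally: "we rely on leave-one-subject out nested cross-validation for assessing the statistical relevance of the resulting models". It also says that finding and validating biomarkers needs training and test data, but no separate test set is defined.

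**The concern.** The endpoint and the final selection criterion are different quantities. The AUC summarises the whole ROC curve. Sensitivity and specificity belong to one point on it, and raising one by moving the cut-off lowers the other. Being highest on both is therefore not a defined rule until the cut-off is fixed.

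The usual way to fill that gap is to take the best-looking point on the observed curve and quote its sensitivity and specificity. That is optimistic because the cut-off has been fitted to the noise in the same persons. It happens with a single biomarker named in advance, so it is separate from the problem of picking the best of many. It also survives a cross-validated choice of biomarker if the cut-off is still set on everyone. Holm correction protects P values and does nothing for these two measures.

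At stake are the figures that the article links to clinical use, which readers would carry into later studies.

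**Working it through.** **The plan's own figure.** The article gives no target for AUC, sensitivity or specificity and no cut-off. Its one precision statement (Project Population) is a smallest detectable correlation of 0.25 with n = 120, 80% power and P = .05. Fisher's z gives r = tanh((1.960 + 0.842)/√117) = tanh(0.259) = 0.253, so the figure reproduces. It says nothing about accuracy at a cut-off.

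**Inputs.** From the article: 120 persons. Assumed, because the article does not give them: the number of persons counted as cases, the true AUC, normal scores with equal variance in both classes, one independent unit per person, and a cut-off that maximises the Youden index J = sensitivity + specificity − 1. The article does not name the Youden index; it stands in for being highest on both.

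**Method.** Simulate one pre-fixed biomarker with mean difference d = √2·Φ⁻¹(AUC). Choose the cut-off c that maximises J in the sample. Compare the apparent values with the true ones at that cut-off: sensitivity 1 − Φ(c − d) and specificity Φ(c).

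**Results** (300 replicates per row; sums may differ by 0.001 through rounding):

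| Cases / non-cases | True AUC | Apparent sens, spec, J | True sens, spec, J | Excess sens, spec, J |
|---|---|---|---|---|
| 20 / 100 | 0.70 | 0.714, 0.673, 0.387 | 0.612, 0.653, 0.265 | 0.102, 0.020, 0.122 |
| 40 / 80 | 0.70 | 0.671, 0.691, 0.362 | 0.612, 0.656, 0.269 | 0.059, 0.035, 0.093 |
| 60 / 60 | 0.70 | 0.661, 0.694, 0.356 | 0.617, 0.653, 0.270 | 0.044, 0.041, 0.086 |
| 40 / 80 | 0.90 | 0.839, 0.845, 0.684 | 0.795, 0.825, 0.620 | 0.044, 0.020, 0.064 |
| 60 / 60 | 0.90 | 0.827, 0.848, 0.674 | 0.801, 0.819, 0.620 | 0.026, 0.029, 0.054 |

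A longer run of 6000 replicates puts the excess in J in the last row at 0.060. With 24 to 42 cases (20–35%) and AUC 0.65–0.75, the excess in J is 0.08–0.12. With 60 cases and AUC 0.75–0.90 it is 0.06–0.08. Half of J's excess is the average per measure, so 0.06–0.12 means 3 to 6 points on average. A single measure can be off by more: with 24 cases and AUC 0.75, sensitivity is 0.739 apparent against 0.649 true, which is 9 points. It can also be off by less: about 2 points for specificity when non-cases are many.

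**Knees instead of persons.** With 240 fully independent knees the excess in J (20–35% diseased, AUC 0.65–0.75) is 0.06–0.08. Knees of one person are not fully independent, so this is a favourable bound.

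**What is not inflated.** In the AUC 0.70 rows the mean observed AUC is 0.700 to 0.701, so the endpoint itself shows no such bias for a pre-fixed biomarker.

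**What held-out cut-offs do.** In the 40 / 80, AUC 0.70 row, setting the cut-off with each person left out gives J = 0.296, against 0.362 apparent and 0.269 true. Most of the excess goes: (0.362 − 0.296)/(0.362 − 0.269) = 0.066/0.093, about 70%.

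**For scale.** Choosing the best of several equally good candidates is a larger, separate source. In the same setting apparent J is 0.483 for the best of 10 and 0.523 for the best of 30, against a true J of about 0.28.

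**The case against.** The strongest reply is that the point rests on silence. This is a condensed article, and how a cut-off is picked may stand in the full protocol or analysis plan. The Introduction's commitment to nested cross-validation is not limited to multi-feature models. The Discussion also enters demographic and baseline health data as covariates, so every single biomarker might sit in a multivariable model that the cross-validation covers. The clause on sensitivity and specificity may be a loose way of saying best ROC performance. The study is exploratory, promises open code and calls for validation at other centres.

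Much of this stands, and it limits the claim:

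- A reader might infer that the reported accuracy **is** too high. The documents do not support that: nowhere do they say that the cut-off is set and judged in the same data. For combinations, the planned nested cross-validation gives held-out accuracy provided the cut-off is set inside the training folds.
- A reader might infer that the excess falls mostly on sensitivity. That depends on an assumed low proportion of cases, because the smaller class bears the larger error. With 60 / 60 at AUC 0.70 the split is 0.044 and 0.041.
- A reader might infer that the two criteria would pick materially different biomarkers. The names do differ often, in 30%, 38% and 43% of simulated studies with 20, 50 and 100 candidates. But the winner on J has a true AUC only 0.002 to 0.004 below that of the winner on AUC, so they are near-ties.

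What does not stand is that the point is merely left to another document. The article itself states a final criterion that differs from its endpoint, and itself ties the held-out procedure to multivariate models. The reading through covariates is possible but not stated.

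**Conclusion.** The concern holds in conditional form. The article pairs a cut-off-free endpoint with a cut-off-dependent final choice, and its wording leaves sensitivity and specificity of individually evaluated biomarkers without stated held-out protection. The same applies to combinations if their cut-off is set outside the training folds. If cut-offs were then chosen and judged in the same 120 persons, J would be too high by about 0.06 to 0.12, or roughly 3 to 9 points on a measure (nearer 2 for one that rests on a large class).

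The size rests on 24 to 60 cases, a true AUC of 0.65 to 0.90, binormal scores and a Youden cut-off, all assumed. The bias is modest for an exploratory study. It is worth correcting because the figures are described as meant for clinical use and the remedy needs no new data.

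**What to change.** - **Principal Findings:** select parameters on one criterion, the held-out AUC, and drop sensitivity and specificity as a selection rule.
- **Feature Analysis and Multivariate Modeling:** extend the leave-one-subject-out nested cross-validation to single biomarkers as well as combinations. State that any cut-off is set inside the training folds, for example at a specificity fixed beforehand, and that sensitivity and specificity are reported only from held-out persons.

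The cost is a few sentences and a few lines of code, with no further data. Analysis was still ongoing when the article was written. The downside is that the reported sensitivity and specificity will look less favourable.
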